***Outcomes***

The primary outcome of the study is sexual self-care which will be measured through the sexual self-care in women of reproductive age (FSHS) questionnaire. The secondary outcome of the study will be participants’ perceived Susceptibility, severity, benefits, barriers, and self-efficacy regarding sexual self-care which will be measured through the researcher-designed questionnaire based on the HBM.

***Educational Intervention***

The constructs of the HBM are outlined as follows (Table 1):

1. **Perceived Susceptibility:** This refers to an individual's belief about the likelihood of experiencing a health threat or developing a health problem. Since infection with human papillomavirus (HPV) can affect individuals' functioning, assessing perceived susceptibility and providing the necessary education can bring about changes in this construct.
2. **Perceived Severity:** This construct addresses the seriousness, severity, and gravity of the disease or problem. Individuals’ understanding of the issues related to being infected with HPV and the resulting complications varies. In this dimension, the extent of problems and symptoms will be identified.
3. **Perceived Benefits:** When an individual acknowledges that they might suffer from the complications of this infection, they will adopt the suggested behavior and engage in actions that provide the most benefit, which encourages consistent participation in educational sessions.
4. **Perceived Barriers:** This construct encompasses the negative aspects that discourage a person from engaging in the recommended behavior. These negative aspects may include the costs involved, discomfort, inconvenience, time consumption, perceived inappropriateness, futility, and lack of self-esteem and dignity.
5. **Self-Efficacy:** An individual infected with HPV faces multiple challenges and complications. Overcoming these problems is a crucial factor in the continuation of the health behavior taught. Since acting based on an individual's incorrect judgment of their personal abilities can lead to undesirable outcomes, an accurate assessment of personal abilities is of high practical value and leads to self-efficacy in behavior.

**Table 1. Health Belief Model-Based Educational Intervention**

| **Session** | **Main Objective** | **Educational Content** | **Teaching Methods and Schedule** |
| --- | --- | --- | --- |
| First | Improve awareness about HPV and sexual self-care | PowerPoint presentation, Session 1 handout | 1) Introduction of the facilitator and participants, study objectives (10 min) 2) Information on HPV, its global and local prevalence, and the importance of sexual self-care (40 min) 3) Q&A session (10 min) |
| Second | Impact on perceived susceptibility, perceived severity, and perceived benefits of the Health Belief Model | PowerPoint presentation, Session 2 handout | 1) Review of the previous session (5 min) 2) Explanation of the consequences of not having a Pap smear test, non-vaccination against non-infecting strains, effects on marital life and quality of life, issues with having multiple sexual partners (45 min) 3) Q&A session to address perceived benefits (10 min) |
| Third | Impact on perceived barriers and self-efficacy of the Health Belief Model | PowerPoint presentation, Session 3 handout, Educational video | 1) Review of previous sessions (5 min) 2) Request women with HPV to share their issues since the onset of symptoms or diagnosis, discuss the concept of sexual self-care and its connection to self-efficacy (40 min) 3) Share common experiences and solutions with each other, summarize the taught materials using the educational video (15 min) 4) Q&A session (10 min) |
| Fourth | Impact on cues to action and performance of the Health Belief Model | PowerPoint presentation, Session 4 handout, Educational video, Role-playing | 1) Review of previous sessions (5 min) 2) Teach various sources of information about HPV (15 min) 3) Ask women to express their fears about symptoms and provide self-care recommendations, advise appropriate behaviors, and communicate problems and needs to healthcare providers (30 min) 4) Role-playing, educational video, and summarization of the taught materials (10 min) 5) Q&A session (10 min) |

***Intervention Design***

The educational intervention will be conducted by the researcher in 4 in-person sessions, each lasting 45-60 minutes, once a week with groups of 10-15 participants. The intervention will be based on the Health Belief Model. Educational methods in this study will include lectures, group discussions, Q&A sessions, PowerPoint presentations, pamphlets, educational videos, and role-playing. The control group will receive routine care. The Sexual Self-Care and HBM questionnaires will be administered to participants in both groups at three points: before the intervention, immediately after, and 8 weeks following the completion of the intervention. To address ethical considerations, the control group participants who wish to receive the education will be provided with pamphlets and educational CDs after the intervention is completed.

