According to the results of a qualitative study conducted in Iran (2023), most women infected with HPV lacked sufficient knowledge about the virus, including its causes, symptoms, complications, prevention, and screening methods. Education, counseling, support, and healthcare services were identified as the main needs and challenges in reproductive and sexual health [17]. Based on the literature review, most studies have focused on the prevention of HPV infection. However, individuals who are already affected by this condition face numerous challenges, highlighting the need for further research into self-care practices for this group of patients. Given the Iranian and Islamic cultural context, HPV infection may be associated with negative psychological effects and significant challenges for Iranian women due to its sexual nature and the stigma attached to it, complicating efforts to educate, support, and address their needs [18,19]. Therefore, the present study aims to examine the impact of an educational intervention based on the Health Belief Model on sexual self-care among women of reproductive age infected with HPV.

**Hypothesis:** The educational intervention based on the Health Belief Model will lead to changes in perceived susceptibility, severity, benefits, barriers, and self-efficacy among women with HPV. These changes will, in turn, modify individual behavior and enhance sexual self-care in those affected by this disease.

**Objectives:** The primary objective of this study is to evaluate the effectiveness of an educational intervention based on the Health Belief Model on sexual self-care among women infected with the HPV. The secondary objectives of the study are:

1. To determine and compare the sexual self-care scores among women with HPV in the intervention and control groups before, immediately after, and 8 weeks following the intervention.
2. To determine and compare the items of the Health Belief Model (perceived susceptibility, perceived severity, perceived benefits, perceived barriers, cues to action, and self-efficacy) regarding sexual self-care among women with HPV in the intervention and control groups before, immediately after, and 8 weeks following the intervention.

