***Sampling method***

After the study proposal is approved by the Ethics Committee of Tehran University of Medical Sciences, and after obtaining a Clinical Trial Registration Code (IRCT) and a written letter of introduction, eligible women will be enrolled in the study. Ethical conditions and considerations will be explained, and written informed consent will be obtained from those willing to participate. The researcher will first provide detailed information about the study, including its title, objectives, inclusion criteria, and the study's procedures. Participants will then be randomly assigned to either the intervention or control group using block randomization. Specifically, volunteers who agree to participate will be randomly allocated to the intervention or control groups using a block size of four. The educational intervention will be conducted in person. The intervention group will receive training based on the Health Belief Model, focusing on its constructs, in four sessions of 45-60 minutes each, held once a week with groups of 10-15 participants. This training will be provided by the researcher. The control group will receive routine care. The questionnaires will be administered to participants in both groups at three time points: before the intervention, immediately after, and 8 weeks post-intervention. To adhere to ethical considerations, the control group, if interested in receiving the training, will be provided with educational pamphlets and CDs after the intervention is completed. Figure 2 shows the schedule of enrolment, intervention, and assessment.

Figure 2. Schedule of enrolment, interventions, and assessments

|  | **STUDY PERIOD** | | | | | | | |  |
| --- | --- | --- | --- | --- | --- | --- | --- | --- | --- |
|  | **Enrolment** | **Allocation** | **Post-allocation** | | | | **Close-out** | |  |
| **TIMEPOINT**** | ***-t_1_*** | **0** | ***t_1_*** | ***t_2_*** | ***t_3_*** | ***t_4_*** | | ***t_5_*** | |
| **ENROLMENT:** |  |  |  |  |  |  | |  | |
| **Eligibility screen** | X |  |  |  |  |  | |  | |
| **Informed consent** | X |  |  |  |  |  | |  | |
| ***Randomized by independent person*** | X |  |  |  |  |  | |  | |
| **Allocation** |  | X |  |  |  |  | |  | |
| **INTERVENTIONS:** |  |  |  |  |  |  | |  | |
| ***Group A: educational intervention*** |  |  |  |  |  |  | |  | |
| ***Group B: control*** |  |  |  |  |  |  | |  | |
| **ASSESSMENTS:** |  |  |  |  |  |  | |  | |

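### Controls may be given the education pamphlets and CDs once the sessions end, before their 8-week assessment, which would contaminate the follow-up comparison

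*Protocol*

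**What the plan says.** Protocol, Intervention Design, describes the intervention as a course delivered "in 4 in-person sessions, each lasting 45-60 minutes, once a week with groups of 10-15 participants". Its methods are "lectures, group discussions, Q&A sessions, PowerPoint presentations, pamphlets, educational videos, and role-playing". For the comparator it states: "The control group will receive routine care".

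The same paragraph schedules the questionnaires in both groups "before the intervention, immediately after, and 8 weeks following the completion of the intervention". The next sentence says that control women who want the education will be "provided with pamphlets and educational CDs after the intervention is completed". The Sampling method section has the matching rule: controls who are interested "will be provided with educational pamphlets and CDs after the intervention is completed".

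The objectives, at the end of the Background, use all three time points. Sexual self-care scores, and separately the Health Belief Model constructs, are to be compared "in the intervention and control groups before, immediately after, and 8 weeks following the intervention". The Outcomes section names the FSHS score as primary without choosing one of these time points.

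**The concern.** The 8-week clock and the release of materials to controls start from the same event. Read as written, a control woman who asks can have pamphlets and a CD at any point in the 8 weeks before her last questionnaire. She would then no longer be a routine-care control, because she holds part of what the other arm was given.

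The 8-week comparison is the one that tells whether the effect lasts. If some controls improve because of the materials, the difference between groups shrinks. A small or null difference at 8 weeks could then mean that the effect had faded or that the controls had caught up, and the data would not separate the two. Access is by request, so uptake is self-selected and may be concentrated in women already inclined to improve their self-care. The protocol does not ask for this access to be recorded, so the analysis could not describe the problem afterwards, let alone correct it.

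**Working it through.** **Timing**

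| Event | Anchor in the protocol |
| --- | --- |
| Intervention | four weekly sessions |
| Second questionnaire | immediately after the intervention |
| Materials offered to controls | after the intervention is completed (Intervention Design; Sampling method) |
| Third questionnaire | 8 weeks after the intervention is completed |

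The intervention is defined as the course of sessions, and the sentence on questionnaires separates its completion from the 8-week point. On that meaning, the earliest permitted release falls about 8 weeks before the third questionnaire.

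**Overlap of content.** Pamphlets and educational videos are among the listed teaching methods. Table 1 puts a handout in each of the four sessions and an educational video in sessions three and four. What is on the CDs is not described.

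**The plan's own figure.** Inputs from the Sample Size section: two-sided alpha 0.05 (z = 1.96), power 80% (z = 0.84), d = 0.7. With the usual two-group formula,

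n = 2 × (1.96 + 0.84)² / 0.7² = 2 × 7.84 / 0.49 = 32 per group,

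which matches the stated 32. A 10% dropout allowance takes the plan to 35 per group.

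**Effect of contamination.** Let c be the share of controls who use the materials before week 8 and f the fraction of the programme's effect that the materials give them. Both are assumptions. The average control gains c × f of the effect, so, with the standard deviation unchanged,

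d(observed) = 0.7 × (1 − c × f).

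Power is that of a two-sided two-sample t-test with 32 evaluable women per group (62 degrees of freedom, noncentrality d × √(32/2) = 4d):

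| c | f | d(observed) | 4d | Power |
| --- | --- | --- | --- | --- |
| 0 | – | 0.700 | 2.80 | 79% |
| 25% | 25% | 0.7 × 0.9375 = 0.656 | 2.63 | 73% |
| 50% | 25% | 0.7 × 0.875 = 0.613 | 2.45 | 67% |
| 50% | 50% | 0.7 × 0.75 = 0.525 | 2.10 | 54% |
| 100% | 50% | 0.7 × 0.50 = 0.350 | 1.40 | 28% |

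The normal approximation, which underlies the protocol's formula, gives slightly higher values for the same rows: 80%, 75%, 69%, 56% and 29%.

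**The case against.** The wording sets an earliest time, not a hand-out date. In both sections the sentence follows the list of all three assessments, so it can be read as a courtesy after the study. The authors may well have meant that. The protocol also does not say in so many words that routine care must continue unchanged to week 8, so this is not a flat contradiction. The materials are only part of a programme built on group sessions, discussion and role-play, and only women who ask receive them. The values of c and f have no source in the protocol, and full uptake is hard to square with an offer made on request. The immediate post-intervention comparison is unaffected if release follows that questionnaire. The bias runs towards no difference, so it would not manufacture a benefit, and a positive 8-week result would remain credible.

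Most of this stands, and it limits the likely size: with c = f = 25% the loss is about 5 percentage points of power. It does not remove the flaw. The post-study reading gives completion of the intervention two meanings in adjacent sentences, and neither section states it. Staff who released the materials in the week after the last session would be complying with the protocol. Even the safe position of the immediate assessment depends on an order of events that is not written down.

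**Conclusion.** The concern holds. The release rule as written allows control women to receive components of the intervention before the 8-week questionnaire, and nothing in the protocol prevents it. The comparison at risk is a stated objective for both the primary outcome and the Health Belief Model constructs.

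The expected bias is towards no difference at 8 weeks, on the assumption that the materials help to some degree. Its size cannot be derived from the protocol. Over the assumed range, the effect falls from d = 0.70 to between 0.66 and 0.35, and power with 32 per group from 79% to between 73% and 28%. The lower end assumes that every control uses the materials, so it is a bound rather than a forecast. The sample size has no allowance for contamination; the increase from 32 to 35 covers dropout only. This should be corrected before any materials are released, because analysis cannot restore the lost contrast.

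**What to change.** In both Intervention Design and Sampling method, change the release point so that pamphlets and CDs are offered to a control participant only after her 8-week FSHS and Health Belief Model questionnaires are complete. It would also help to record any earlier access to the materials, so that accidental contamination can be reported.

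The cost is one phrase in two places. Interested controls wait about 8 weeks longer for optional material while routine care continues, and the offer to them is kept. With the contrast protected, d stays at the planned 0.7 and no sample-size figure changes. If release after the final assessment was always intended, the edit only makes that explicit.

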***Study instruments***

The three study instruments are explained in what follows.

**-****Demographic and obstetric information questionnaire**: It consists of 16 questions including: Age, Spouse's Age, Education Level, Spouse's Education Level, Employment Status, Spouse's Occupation, Income Level, Duration of Marriage, Number of Pregnancies, Number of Deliveries, Type of Delivery, Number of Abortions, Contraceptive Method, History of Pap Smear, History of HPV Vaccination, Duration of HPV Infection Based on Diagnostic Tests.

-**The Sexual Self-Care in Women of Reproductive Age (****FSHS) questionnaire**: It consists of 40 items scored on a 5-point Likert scale ranging from Never (1) to Always (5) across 4 domains: prevention of sexually transmitted infections (STIs), prevention of gynecological cancers, prevention of unintended pregnancies, and promotion of sexual health. Developed using a deductive approach based on the Waltz model in 2021 by Yazdani and colleagues in Iran, the tool has demonstrated a content validity index (CVI) of 0.93, a content validity ratio (CVR) of 0.96, and a high internal consistency reliability with a Cronbach's alpha of 0.94. The stability of the instrument, measured by intra-cluster correlation, was 0.97 (confidence interval: 0.94-0.98), indicating strong validity and reliability in the Iranian population, making it a suitable measure of sexual self-care [24].

**-Researcher-Designed Questionnaire Based on the Health Belief Model**: This questionnaire is designed by researchers based on the study objectives and relevant literature. The questions are shown in Table 2. To confirm the qualitative content validity of the questionnaire, it will be reviewed by 10 faculty members in midwifery and reproductive health at Tehran University of Medical Sciences, and their feedback will be incorporated. For the CVR, experts will be asked to evaluate each item on a 3-point scale (essential, useful but not essential, not essential). After calculating the CVR and making necessary revisions, experts will also assess the CVI by rating each item on a scale from 1 to 4 based on relevance (4 = very relevant, 3 = relevant, 2 = somewhat relevant, 1 = not relevant). Face validity will be assessed by asking 10 women of reproductive age to provide feedback on the clarity of the questionnaire, and necessary clarifications will be made based on their input. Internal consistency will be evaluated using Cronbach's alpha to determine the reliability of the instrument.

**Table 2. Researcher-Designed Questionnaire Based on the Health Belief Model**

| **Question Type** | **Questions** | **Scale** |
| --- | --- | --- |
| Perceived Susceptibility | 1. I am at risk of complications from HPV. 2. I am at risk of cervical cancer. 3. I am at risk of high-risk HPV strains. 4. My partner is at risk of the disease. | 5-point Likert scale (1=Strongly disagree, 5=Strongly agree) |
| Perceived Severity | 1. The disease causes problems in sexual relations. 2. Thinking about the complications of HPV scares me. 3. Thinking about the problems caused by HPV infection makes me anxious and worried. 4. If I experience HPV complications, my spouse and family will blame me. 5. The cost of treatment is high. 6. Quality of life decreases after contracting the disease. | 5-point Likert scale (1=Strongly disagree, 5=Strongly agree) |
| Perceived Benefits | 1. Women who engage in sexual self-care experience fewer physical and emotional crises. 2. Sexual self-care reduces the costs associated with cervical cancer. 3. Sexual self-care prevents my partner from contracting the disease. 4. Sexual self-care allows me to enjoy sexual relations more. 5. Sexual self-care helps prevent high-risk HPV strains. | 5-point Likert scale (1=Strongly disagree, 5=Strongly agree) |
| Perceived Barriers | 1. I don't have enough time to get the HPV vaccine. 2. I don't have enough time to visit a doctor or midwife. 3. I can't afford the HPV vaccine. 4. I don't have access to accurate information about sexual self-care. 5. My partner agrees to use condoms during sexual relations. 6. I feel embarrassed about vaginal exams and Pap smears. 7. I am afraid of vaginal exams and Pap smears. 8. Fear of side effects from the HPV vaccine prevents me from getting it. | 5-point Likert scale (1=Strongly disagree, 5=Strongly agree) |
| Self-Efficacy | 1. Reading brochures and using educational videos are effective for sexual self-care. 2. Media (TV and social media) are effective for sexual self-care. 3. My doctor and midwife assist me with sexual self-care. | 5-point Likert scale (1=Strongly disagree, 5=Strongly agree) |

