Self-care refers to the ability of individuals, families, and communities to take intentional and purposeful actions to promote and maintain their health, prevent illness, and manage disease and disability, with or without the support of healthcare providers [12]. Effective techniques for enhancing self-care behaviors in women are organized into three categories: lifestyle modification, preventive behaviors and screening, and disease and treatment management behaviors. Self-care behaviors that help prevent HPV infection include undergoing Pap smears, vaccination, consistent and correct use of condoms during sexual intercourse, and limiting sexual partners to one [11,12]. Self-care interventions are among the most important and promising approaches to improving universal health coverage and well-being, both for health systems and individuals. As accessible, cost-effective, and acceptable interventions, they promote self-efficacy, independence, and participation in health [13], yet nearly four billion women of reproductive age worldwide lack access to such services [14].

One of the most widely used theories in health behavior is the Health Belief Model (HBM), which has extensive applications in health education for various health-related issues. The HBM posits that six constructs predict health behavior: perceived susceptibility, perceived severity, perceived benefits, perceived barriers, self-efficacy, and cues to action [15]. A study by Bayrami et al. (2019) aimed to assess the constructs of the HBM in relation to the willingness to receive HPV vaccination among female students at Urmia University of Medical Sciences. According to the results, perceived susceptibility, perceived severity, perceived benefits, perceived barriers, self-efficacy, and cues to action were all significantly associated with the acceptance of the HPV vaccine [16].

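### Secondary objective 2 promises six Health Belief Model constructs but the questionnaire scores five: cues to action has no score, the self-efficacy items do not ask about the woman's own ability, and one barrier item is worded in the opposite direction

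*Protocol*

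**What the plan says.** The Protocol's Background states that in this model "six constructs predict health behavior". Secondary objective 2 follows that count. Its list names cues to action and self-efficacy separately ("perceived barriers, cues to action, and self-efficacy) regarding sexual self-care among women with HPV") and compares the groups at three time points. In Table 1 the aim of session 4 is "Impact on cues to action and performance of the Health Belief Model".

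The Outcomes section defines the secondary outcome as "perceived Susceptibility, severity, benefits, barriers, and self-efficacy regarding sexual self-care", which is five constructs. The numbered definitions under Educational Intervention cover the same five, and so does Table 2.

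Table 2 puts three items under Self-Efficacy. The first is "1. Reading brochures and using educational videos are effective for sexual self-care"; the others ask whether media are effective and whether the doctor and midwife assist. Under Perceived Barriers it lists eight items, of which the fifth is "5. My partner agrees to use condoms during sexual relations". Every item uses the same 1 to 5 agreement scale, and the Protocol states no scoring rule for any subscale. The section on study instruments describes content validity, face validity and Cronbach's alpha for this questionnaire as steps still to come.

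**The concern.** There are three separate faults, of different strength.

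- **Missing construct.** One construct that the objective promises, and that a whole session is meant to change, has no score.
- **Label and content.** A result reported as self-efficacy would describe views on information sources and professional help, not confidence in one's own ability.
- **Direction of one item.** The Protocol describes barriers as things that put a person off the behaviour. A partner's agreement to condoms is the absence of such a thing. If the item is added as printed, a woman whose partner comes to agree moves up the barrier score.

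The Discussion says the study will identify the construct that matters most for sexual self-care and will use this to shape later programmes. That ranking depends on the affected scores. The hypothesis also names barriers and self-efficacy among the routes by which the education is expected to work.

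**Working it through.** The Protocol gives no figure for the Health Belief Model questionnaire, so there is none to reproduce. The sample size calculation does not depend on it.

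**1. Constructs, place by place**

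| Place in the Protocol | Constructs | Cues to action included? |
|---|---|---|
| Background, description of the model | 6 | yes |
| Secondary objective 2 | 6 | yes |
| Table 1, session 4 | target of the session | yes |
| Hypothesis | 5 | no |
| Outcomes | 5 | no |
| Definitions under Educational Intervention | 5 | no |
| Table 2 | 5 | no |

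Six are promised and five are scored.

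**2. The three Self-Efficacy items**

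The definition under Educational Intervention ties self-efficacy to a correct judgment of one's personal abilities. Items that ask about own ability: 0 of 3. The nearest match in the Protocol is session 4, which includes "Teach various sources of information about HPV (15 min" minutes) and communication with healthcare providers.

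The possible readings are:
- If the items are cues to action, that construct is measured under the wrong label and self-efficacy has no items.
- If they are neither, both constructs have no items.
- If they are accepted as self-efficacy despite the definition, cues to action still has no items.

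On every reading at least one of the six constructs has no items.

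**3. Barrier item 5, if it is summed unreversed**

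Inputs from Table 2: 8 items scored 1 to 5, of which 7 are worded so that agreement means a barrier and 1 the other way.

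- Correctly keyed, no barriers scores 8 × 1 = 8 and maximal barriers 8 × 5 = 40, a span of 32.
- As printed, no barriers scores 7 × 1 + 5 = 12 and maximal barriers 7 × 5 + 1 = 36, a span of 24.
- Raw change shown under an equal shift on all items: (7 − 1)/8 = 24/32 = 75%.

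A comparison between groups depends on the standardised effect, so the variance is needed too. The Protocol gives no inter-item correlation r. I assume a common r of 0.2 to 0.5 and unit item variances.

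- Variance of the correctly keyed sum: 8 + 56r.
- Variance with one item reversed: 8 + (42 − 14)r = 8 + 28r.
- Standardised effect retained: 0.75 × √[(8 + 56r)/(8 + 28r)].
- Alpha: (8/7) × (1 − 8/variance of the sum).

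| r (assumed) | Variance, keyed | Variance, as printed | Alpha, keyed | Alpha, as printed | Standardised effect retained |
|---|---|---|---|---|---|
| 0.2 | 19.2 | 13.6 | 0.67 | 0.47 | 89% |
| 0.3 | 24.8 | 16.4 | 0.77 | 0.59 | 92% |
| 0.4 | 30.4 | 19.2 | 0.84 | 0.67 | 94% |
| 0.5 | 36.0 | 22.0 | 0.89 | 0.73 | 96% |

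The variance shrinks along with the shift, so the loss in standardised effect is much smaller than the raw 25%.

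**The case against.** **The item 5 harm is conditional.** Scoring rules are commonly left to an analysis plan or scoring manual, which is not shown. A mixed-direction item is harmless once reversed, and a negation may have been lost in translation. This stands: a reader might infer that the barrier score is certainly wrong, and the documents do not show that. It does not help the other two parts, because no scoring rule can create a missing subscale or turn the three items into questions about own ability.

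**The questionnaire is a draft.** Ten faculty members will review it and revisions will follow, and a low alpha could expose item 5. This is partly right. However, the content validity ratings go item by item. An item can be rated essential and relevant and still point the wrong way, and ratings of listed items do not ask what is absent. Nor does alpha test whether a label fits its items. Free comments might catch all three faults, but nothing in the plan makes sure of it.

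**Calling the three items cues to action is a judgment.** This stands. The Protocol never defines that construct, and two of the items ask whether something is effective, which is a belief and not clearly a prompt. The firm statement is the negative one: they do not fit the Protocol's own description of self-efficacy.

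**The mismatch could be settled the other way.** Cues to action could be dropped from objective 2, since the hypothesis, outcomes, definitions and Table 2 already use five constructs. That would make the lists agree, but it would leave the target of session 4 unmeasured and the self-efficacy label still wrong.

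**The 75% overstates the loss.** It is a raw-score figure and needs an equal shift on all eight items, including affordability of the vaccine, which education may not move. This stands, and the standardised figures should be read beside it.

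**Conclusion.** The point holds for secondary objective 2 and for the ranking of constructs. Two parts rest on the text alone: six constructs are promised and five scored, and none of the three Self-Efficacy items asks about own ability. As the plan stands, the cues-to-action result would be absent and the self-efficacy result would carry the wrong name.

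The third part is conditional. If item 5 is not reversed, the barrier score shows 75% of the true raw change under an equal shift and about 89% to 96% of the standardised effect. Alpha falls, for example from 0.77 to 0.59 at r = 0.3. The standardised effects and the alphas rest on assumed correlations.

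A reader might infer that objective 2 cannot be answered at all. The documents do not support that: susceptibility, severity and benefits can be compared as they are, and barriers can be compared once item 5 is settled. The primary outcome, sexual self-care on the FSHS, is not affected. The matter should be corrected, but it does not threaten the main result.

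**What to change.** Before the expert validity review and before baseline data are collected:

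1. Reword barrier item 5 as a barrier, or state that it is reverse-scored.
2. Add a few items on the woman's own ability or confidence under Self-Efficacy.
3. Put the three existing items to the expert panel as candidate cues-to-action items, and label them so only if the panel agrees.
4. Use the same construct list in secondary objective 2, Outcomes, the definitions under Educational Intervention and Table 2.

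The cost is a slightly longer form and some editing. The Protocol describes validation in the future tense but does not say whether recruitment has begun. If baseline collection is already under way, new items would have no baseline value. In that case, reverse-score item 5, do not report the three items as self-efficacy, and restrict objective 2 and the ranking to the constructs actually measured.
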